**Figure 4 F4:**
[figure not shown]
Summary of methods used in the extended physiology sub-study. RFR, resting full cycle ratio; FFR, fractional flow reserve; CFR, coronary flow reserve; MRR, microvascular resistance reserve; f, viscous friction losses; s, separation losses; Q, volumetric flow; ΔP, pressure gradient between the proximal and distal coronary pressure; Pd, distal coronary pressure.

A substudy of the register is planned to achieve extended physiological assessment in patients with the suspicion of microvascular disease in line with the latest ESC guideline stressing the role of microcirculatory dysfunction in the adverse outcome events in patients with non-significant coronary stenoses by FFR (class IIa, level B recommendation) (2).

In the extended physiological assessment, 3 parameters are calculated:

Pressure bounded CFR interval (pbCFR)

According to the intracoronary average pressure values, the pbCFR interval will be calculated with the formula (11):

$$\begin{array}{l} \sqrt{\frac{Hyperemic\text{ Δ}p\;}{Resting\text{ Δ}p}}\leq pbCFR\leq \frac{Hyperemic\text{ Δ}p}{Resting\text{ Δ}p} \end{array}$$

If the cut-off value CFR = 2 lies inside the defined pbCFR interval, then a novel CFR calculation based on three-dimensional reconstruction and simple flow dynamic modeling will be performed to get the exact CFR_p−3D_ value to diagnose or exclude microvascular disease.

Pressure and 3D derived CFR (CFR_p−3D_)

Hemodynamic calculations can be used that combines intracoronary pressure data and 3D anatomical parameters. The results of 3D angiographic reconstruction from the selected two angiograms and the hyperemic and resting pressure data are the basis of the simple hemodynamic equations calculating the ratio of the hyperemic and resting flow (CFR_p−3D_) (13, 14).

CFR_p−3D_/FFR index

One simple possibility for the characterization of the microvasculature is to define the CFR_p−3D_/FFR index. If this value is below 2, the result indicates impaired microvascular vasodilator capacity (12, 13).

Microvascular resistance reserve (MRR)

For getting more precise microvascular parameters, flow modeling using the data of the 3D coronary reconstruction and the intracoronary pressure values provide the microvascular resistance reserve (MRR) as detailed in the Figure 4 (13).

Vasodilatation is induced by intracoronary adenosine injection to determine the FFR value (left upper panel). For calculating a specific CFR and MRR values (CFR_p−3D_ and MRR_p−3D_) hemodynamic calculations are used that combines intracoronary pressure data and 3D anatomical parameters (left lower panel). Offline 3D angiographic reconstruction will be performed from the selected two angiograms of good quality, with at least 25° difference in angle, using a dedicated software (e.g., QAngio XA Research Edition 1.0, Medis Specials bv, Leiden).

Based on the hyperemic and the resting pressure data, simple hemodynamic equations calculate the resting and hyperemic flow, the CFR and the MRR (right lower panel). The pressure-flow relation is displayed by our freely available software https://coronart.hu/ in patient-specific flow range (upper middle panel) (13, 14). The CFR _p−3D_/FFR index can be expected to be very close to the calculated MRR value (in this example: 2.30 vs. 2.26, respectively).

The green arrows indicate the flow-chart of the calculations, while the blue arrows show the effect of the different hemodynamical parameters.

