## Abstract

**Background:** The morphology and functional severity of coronary stenosis show poor correlation. However, in clinical practice, the visual assessment of the invasive coronary angiography is still the most common means for evaluating coronary disease. The fractional flow reserve (FFR), the coronary flow reserve (CFR), and the resting full-cycle ratio (RFR) are established indices to determine the hemodynamic significance of a coronary stenosis.

**Design/Methods:** The READY register (NCT04857762) is a prospective, multicentre register of patients who underwent invasive intracoronary FFR and RFR measurement. The main aim of the registry is to compare the visual estimate of coronary lesions and the functional severity of the stenosis assessed by FFR, as well as the RFR pullback. Characterizations of the coronary vessel for predominantly focal, diffuse, or mixed type disease according to visual vs. RFR pullback determination will be compared. The secondary endpoint of the study is a composite of major adverse cardiac events, including death, myocardial infarction, and repeat coronary revascularization at 1 year. These endpoints will be compared in patients with non-ischemic FFR in the subgroup of cases where the local pressure drop indicates a focal lesion according to the definition of ΔRFR > 0.05 (for <25 mm segment length) and in the subgroup without significant ΔRFR. In case of an FFR value above 0.80, an extended physiological analysis is planned to diagnose or exclude microvascular disease using the CFR/FFR index. This includes novel flow dynamic modeling for CFR calculation (CFR_p−3D_).

**Conclusion:** The READY register will define the effect of RFR measurement on visual estimation-based clinical decision-making. It can identify a prognostic value of ΔRFR during RFR pullback, and it would also explore the frequency of microvascular disease in the patient population with FFR > 0.80.

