Such a prognostic pressure-drop cut-off value for invasive hyperemic or non-hyperemic pullback measurements has not yet been established. We defined the focal disease criterion as ΔRFR >0.05 for <25 mm segment length which is the same gradient for a 1 mm unit (>0.002/mm), similarly as it was defined for the iFR. We set out to test this threshold for prognostic value in our registry during the follow-up of patients with negative FFR but positive focal ΔRFR (4).

While the main aim of the READY registry is to characterize the effect of RFR measurement on the visual estimation-based clinical decision-making, it may also provide guidance in cases with a non-ischemic FFR but with focal pressure drop (ΔRFR > 0.05).

We plan to analyze the follow-up data at 1 year not only according to the pre-specified categories but also to determine potential alternative cut-off values using receiver-operator characteristic (ROC) analysis. In addition, it will also explore the frequency of microvascular disease in the patient population with FFR > 0.80.

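### Microvascular disease is gated at CFR = 2 but diagnosed at CFR/FFR < 2, and no shown text says which rule defines the rate in secondary endpoint 4

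*Protocol article*

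**What the plan says.** Secondary endpoint 4 is a rate of microvascular dysfunction. Four places in the protocol article bear on how it is decided.

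- **Extended physiological assessment, pbCFR paragraph.** Two measured pressure drops bound CFR. The next step depends on CFR = 2: "If the cut-off value CFR = 2 lies inside the defined pbCFR interval, then a novel CFR calculation based on three-dimensional reconstruction" (CFRp-3D) is made, to give an exact "value to diagnose or exclude microvascular disease".
- **Same section, CFRp-3D/FFR index paragraph.** The cut-off is applied to the ratio: "If this value is below 2, the result indicates impaired microvascular vasodilator capacity".
- **Abstract, Design/Methods.** For FFR above 0.80, "an extended physiological analysis is planned to diagnose or exclude microvascular disease using the CFR/FFR index".
- **Discussion, after Figure 5.** Microvascular disease is diagnosed when the CFR/FFR index or the MRR is low. No MRR cut-off is given, and the diagnosis is linked to drug treatment.

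Item 4 of the secondary endpoints also plans CFR and MRR from pressures and 3D data in patients with non-pathological FFR, and mentions no gate.

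On the population, the Background wants to "explore the frequency of microvascular disease in the patient population with FFR > 0.80", while the text below Figure 4 places the sub-study "in patients with the suspicion of microvascular disease".

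**The concern.** A threshold of 2 on CFR and a threshold of 2 on CFR/FFR are different rules whenever FFR is below 1, which is nearly everyone in this sub-study. The article attaches diagnostic language to both and sets no precedence in the text shown. The gate is also on a different scale from the index that it feeds, so it can withhold CFRp-3D from a patient whose index is still undecided.

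At stake is the meaning of the reported rate. If the rule stays open, it can be chosen after the data are seen, or two rules can be mixed in one numerator.

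**Working it through.** **No figure to reproduce.** The article states no expected rate, sample size or power for endpoint 4. Steps 1 and 2 use only the document's rules plus one illustrative patient. Steps 3 and 4 rest on stated assumptions.

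**Step 1: the two cut-offs on one scale.** CFR/FFR < 2 ⇔ CFR < 2 × FFR.

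| FFR | 2 × FFR | Positive by CFR < 2, negative by index |
|---|---|---|
| 0.81 | 1.62 | CFR 1.62 to just under 2 |
| 0.85 | 1.70 | CFR 1.70 to just under 2 |
| 0.90 | 1.80 | CFR 1.80 to just under 2 |
| 0.95 | 1.90 | CFR 1.90 to just under 2 |
| 1.00 | 2.00 | none |

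Example: CFR 1.80 with FFR 0.85 gives an index of 1.80/0.85 = 2.12, which is positive by CFR and negative by index. Because 2 × FFR never exceeds 2, the disagreement runs one way only.

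**Step 2: the gate.** Let R = hyperemic Δp / resting Δp. The article's interval is √R to R, so it contains 2 only when 2 ≤ R ≤ 4.

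- R > 4: CFR exceeds 2, so the index does too. Both rules agree.
- R < 2: the whole interval is below 2 and CFRp-3D is not triggered, but the index may still be 2 or more.

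Illustrative patient: FFR 0.82, Δp 18 mmHg hyperemic and 9.5 mmHg resting. R = 18/9.5 = 1.89 and √R = 1.38, so pbCFR is 1.38–1.89 and the gate stays closed. Dividing by 0.82 gives a possible index of 1.68–2.31, which straddles 2.

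**Step 3: how easily the gate misleads.** Assume Δp = fQ + sQ² and let a be the friction share of the resting Δp. Then R = a·CFR + (1 − a)·CFR². For FFR 0.81 and the smallest index-negative CFR, 1.62, R < 2 requires 1.62a + 2.6244(1 − a) < 2, so a > 0.6244/1.0044 = 0.62. The misfit needs a friction-dominated lesion, so its frequency depends on a share that the article does not give.

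**Step 4: size.** Assumptions: log-normal CFR, median 1.8–2.6, log-SD 0.4; FFR mean 0.87–0.90, SD 0.05, truncated to 0.80–1.00; a uniform on 0–1 or on 0.2–0.8.

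| Rule for the endpoint | Excess over CFR/FFR < 2 in everyone |
|---|---|
| CFR < 2 as final rule | about 8–13 points (41% vs 29–31% at median CFR 2.2) |
| Gate at 2, then index where CFRp-3D exists, with R < 2 counted positive | about 0–1.3 points |

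Other assumptions (FFR uniform within 0.81–1.00, median CFR 2.0–3.0, log-SD 0.3–0.4) give about 4–16 points for the first row. In the Step 4 scenarios, 32–39% of patients have an interval containing 2. With a bound of 2 × FFR, the interval straddles when 2·FFR ≤ R ≤ 4·FFR², and 21–35% do.

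**The case against.** The strongest reply is that CFR = 2 is only a triage threshold. The Abstract and the Discussion diagnose by the index (the Discussion also by MRR), and neither diagnoses by raw CFR. On that reading pbCFR screens, the index decides, and the excess is about 0–1.3 points. With an assumed 150 patients above FFR 0.80 and a rate of 30%, the 95% half-width is 1.96 × √(0.3 × 0.7/150) = 7 points, so such an excess would not be noticed. Figures 4 and 5 are not visible and may show the sequence, and the rate is descriptive.

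Much of this stands, and it rules out four stronger readings that a reader might infer:

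- **That a patient with an interval wholly below 2 is declared diseased.** The article says only when CFRp-3D is calculated. The classification of the others is an inference.
- **That the index and MRR do not exist outside the straddling group.** Item 4 plans CFR and MRR in patients with non-pathological FFR without a gate. The passages disagree, and neither reading is established.
- **That the excess is over-diagnosis.** This would take the index as the truth. The article calls it one simple option and MRR more precise.
- **That a suspicion-selected denominator inflates the rate.** Item 4 equates the relevant cases with non-pathological FFR, and the Abstract, Background and Discussion agree. The wording on suspicion is a minor point to align.

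The reply does not remove the conflict. The gate sentence itself carries diagnostic wording, and no shown text ranks it against the index.

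**Conclusion.** The concern holds as a conflict between stated rules for endpoint 4. That the rules classify some patients differently for every FFR below 1, always with the higher rate under CFR < 2, is algebra and needs no assumption. So is the mismatch between the gate and the index.

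The size does need assumptions. It is about 8–13 points if CFR < 2 is the final rule, which would matter for interpretation, and about 0–1.3 points if the gate is followed by the index, which would be small. The second figure would grow if friction dominates the pressure drop. None of the distributions comes from the documents. The endpoint is exploratory and the primary endpoint is untouched, but the rule should be settled before the data are analysed.

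**What to change.** 1. Reconcile the Abstract, item 4 of the secondary endpoints, the extended physiological assessment and the Discussion, so that endpoint 4 has one defining parameter and one cut-off. Which one is for the investigators to decide, because the Discussion ties the diagnosis to treatment.
2. Make the pbCFR triage consistent with that choice. If CFR/FFR < 2 is kept, the equivalent bound for the interval is 2 × FFR. Otherwise calculate CFRp-3D without the gate, as item 4 implies.
3. State how patients classified by pbCFR alone are counted.
4. Report the rate over all patients with FFR > 0.80, showing non-computable cases, and align the wording on suspicion with this.
5. Give the remaining indices as sensitivity analyses, with a stated cut-off for MRR if it is used to classify.

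The cost is a few sentences and offline work, since resting and hyperemic pressures are already recorded and reconstruction is offline. In the scenarios of Step 4, a 2 × FFR bound needs fewer 3D reconstructions (21–35% against 32–39% of patients). Dropping the gate needs one for every patient with FFR > 0.80.

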### Statistical Analysis

Descriptive statistics are planned as mean and SD, median (interquartile range) of the measured RFR and FFR values. Categorical variables will be compared with the Pearson χ^2^ test for focal/ diffuse/mixed type categorizations of the coronary disease by visual and physiological evaluations.

Correlation among variables will be determined by calculating Spearman ρ correlation coefficient.

Kaplan-Meier curves will be used to graphically display adverse events by focal lesion (ΔRFR ≥ 0.05/ 25 mm) and without focal lesion (ΔRFR < 0.05/ 25 mm) arms in the cases with FFR > 0.80. We plan to use survival analytic techniques such as a log-rank test to estimate the difference between the 2 subgroups.

The required sample size for the statistically significant (*p* < 0.05) difference with 80% power of the Kaplan-Meier curves of adverse events by focal lesion (ΔRFR ≥ 0.05/ 25 mm) and without focal lesion arms are 425, assuming 10 and 2% event rate in the two subgroups, respectively.

ROC analysis will be used to determine an optimal clinical cut of value, of ΔRFR (together its sensitivity and specificity) to predict a secondary endpoint at 1 year.

All analyses will be performed by using the Medcalc statistical software (MedCalc Software Ltd, Belgium).

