### Angiographic Evaluation Protocol

Coronary diagnostic angiography is performed according to routine clinical practice. The visual estimate of the diameters stenosis % of the culprit lesion(s) should be included prospectively in the modified Syntax segmentation scheme (https://coronart.hu/), where the corresponding ventricular segments supply is indicated on a polar map (Figure 1). At the same time, the operator is required to record the characteristics of the coronary vessel disease as focal, diffuse, or mixed type, and to document their plan for angioplasty on the basis of the visual assessment.

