**Figure 2 F2:**
[figure not shown]
RFR pullback investigation in the left circumflex artery with intermediate stenoses. Both lesions proved to be significant according to the local ΔRFR.

Our main aim is to compare the visual estimate of coronary lesions and the functional severity of the stenosis assessed by RFR pullback both on lesion and vessel levels.

Primary endpoint:

Characterization of the coronary vessel for predominantly focal/diffuse or mixed type disease according to visual vs. RFR pullback determination.

**Focal disease**: ΔRFR > 0.05 for <25 mm segment length (>0.002/mm)

**Diffuse disease**: ΔRFR > 0.05 for >25 mm segment length

If both the focal and diffuse criteria are fulfilled in the investigated vessel, then mixed type disease is diagnosed (Figure 2).

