**II. Secondary endpoints:**
The therapeutic strategy (conservative/PCI/CABG) will be compared based on visual evaluation vs. RFR measurements (Figure 3).

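### The primary endpoint compares two ratings of the same vessel, but the named test, Pearson chi-square, neither quantifies agreement nor allows for the pairing

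*Protocol article*

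**What the plan says.** The main aim, given under the Invasive Coronary Physiology Assessment Protocol, is worded as follows: "compare the visual estimate of coronary lesions and the functional severity of the stenosis assessed by RFR pullback both on lesion and vessel levels". The primary endpoint that follows is "Characterization of the coronary vessel for predominantly focal/diffuse or mixed type disease according to visual vs. RFR pullback determination".

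Both ratings are made on the same vessel:

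- **Visual.** Under Angiographic Evaluation Protocol, "the operator is required to record the characteristics of the coronary vessel disease as focal, diffuse, or mixed type".
- **RFR pullback.** Under the primary endpoint, focal disease is ΔRFR > 0.05 over less than 25 mm and diffuse disease is ΔRFR > 0.05 over more than 25 mm. For the third type, "If both the focal and diffuse criteria are fulfilled in the investigated vessel, then mixed type disease is diagnosed".

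The Statistical Analysis section names one test for this comparison of the visual with the physiological typing: "Categorical variables will be compared with the Pearson χ^2^ test for focal/ diffuse/mixed type categorizations". The only other measure of relation in that section is Spearman's ρ, which also measures association. The article mentions no kappa, percent agreement, McNemar, Bowker or Stuart-Maxwell analysis.

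**The concern.** When the same units are classified by two methods, there are two natural questions. How often do the methods give the same answer? When they differ, does one method move vessels systematically towards a particular type? Pearson chi-square is built for a different question, namely whether two classifications are independent, or whether two separate samples share a distribution.

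The article does not say which table the test will be run on. There are two candidates: the 3x3 cross-table of visual by RFR type, or a 2x3 table of the visual counts against the RFR counts. Neither gives a valid statement about agreement or reclassification.

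The abstract says that the register will define the effect of RFR measurement on decisions based on visual estimation. A primary p-value that looks the same under near-perfect and under very poor concordance would not tell a reader how often the pullback changes the visual classification, or in which direction.

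**Working it through.** The article gives no sample size, expected agreement or category frequencies for the primary endpoint, so there is no stated figure to reproduce. The tables, margins and kappa values below are assumptions. The 300 is the planned number of patients (Study Objectives and Design), taken here as one vessel each.

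**Reading 1: the 3x3 cross-table (4 df, 5% critical value 9.49)**

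Take 100 vessels in each category for both ratings. Every expected count is then 100 × 100 / 300 = 33.33, and chance agreement is 1/3. Rows are visual, columns are RFR.

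| Assumed table | Agreement | Kappa | Chi-square |
|---|---|---|---|
| A: [90,5,5], [5,90,5], [5,5,90] | 90% | 0.85 | 433.5 |
| B: [5,90,5], [5,5,90], [90,5,5] | 5% | −0.43 | 433.5 |
| C: [10,80,10], [80,10,10], [10,10,80] | 33% | 0.00 | 294 |

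- A and B each have three cells of 90 and six cells of 5. Chi-square = 3 × (90 − 33.33)²/33.33 + 6 × (5 − 33.33)²/33.33 = 289.0 + 144.5 = 433.5 (p about 1.6e-92).
- Kappa for A = (0.90 − 0.333)/(1 − 0.333) = 0.85. Kappa for B = (0.05 − 0.333)/(1 − 0.333) = −0.43.
- C has agreement exactly at chance and is still overwhelmingly significant (p about 2e-62).

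Chi-square ignores which cells lie on the diagonal, so it cannot separate A from B.

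Next, weak but positive agreement. Assume both ratings have margins p = 50/25/25% and cell probabilities (1 − k) × p_i p_j, plus k × p_i on the diagonal, so that kappa = k.

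- Raw agreement = (1 − k) × (0.25 + 0.0625 + 0.0625) + k. At k = 0.15 this is 0.85 × 0.375 + 0.15 = 46.9%. At k = 0.20 it is 50.0%.
- Noncentrality of chi-square = 300 × 2k². At k = 0.15 this is 13.5, and at k = 0.20 it is 24.0.
- The large-sample approximation gives power of 85% and 99%. Direct simulation with 40,000 runs gives 83% and 98%.

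The test would therefore usually be significant although about half of the vessels are typed differently by the two methods.

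**Reading 2: the two sets of margins as a 2x3 table (2 df, critical value 5.99)**

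This counts 300 pairs as 600 independent observations. Under the model above with equal margins:

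- The variance of a difference in category proportions is 2p(1 − p)/n if the samples were independent, but 2p(1 − p)(1 − k)/n for the actual pairs.
- The statistic therefore behaves as (1 − k) times a chi-square on 2 df, and the true type I error is exp(−5.99 / [2(1 − k)]).

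| Kappa | Formula | Simulated, margins chi-square | Simulated, Stuart-Maxwell |
|---|---|---|---|
| 0.2 | exp(−3.74) = 2.4% | 2.3% | 4.9% |
| 0.4 | exp(−4.99) = 0.7% | 0.7% | 4.9% |
| 0.6 | exp(−7.49) = 0.06% | 0.05% | 5.0% |

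The better the methods agree, the less able this version is to detect a real shift between them. Tables A, B and C all have equal margins, so this version gives chi-square 0 and p = 1 for each. It says nothing about agreement.

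**Category sets**

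As defined, the RFR typing gives no category to a vessel with no ΔRFR > 0.05, and none to a segment of exactly 25 mm. The secondary endpoints expect a subgroup without significant ΔRFR, so the first case will occur. The visual rating has three types only. Kappa, Bowker and Stuart-Maxwell need the same categories on both sides, so this must be settled for any agreement analysis.

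**The case against.** **The article says compare, not agree.** This is true. The Background describes the gap as missing data on how visual assessment and RFR relate, and the Discussion speaks of poor correlation. A test of association does address whether a relation exists, and the cross-table behind it would let a reader see concordance. A reader might infer that the planned analysis cannot address the main aim at all. That goes too far: it addresses the aim incompletely, with no measure of concordance, no interval and no test of shift.

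**Details belong in the analysis plan.** That would answer a missing method. Here the article names a specific test for the primary comparison, and that test does not suit paired ratings.

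**The therapy comparison.** The secondary endpoint reads "The therapeutic strategy (conservative/PCI/CABG) will be compared based on visual evaluation vs. RFR measurements" and is also paired. A reader might infer that it too has the wrong test. The Statistical Analysis section ties Pearson chi-square to the vessel types only and names no test for therapy, so no error is stated there.

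**Lesion-level analysis.** The aim mentions lesions, and a reader might infer that several lesions of one vessel would enter tests that assume independence. No lesion-level test is stated, and the primary endpoint is defined for the vessel, so the documents do not support this.

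**The consequence is limited.** This is an observational register with no power calculation for its primary endpoint. The data stay usable, and on the margins reading the error loses power but does not create false positives. All of that stands.

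**Conclusion.** The point holds for the vessel-level primary endpoint. The data are paired and the one test named for them is unsuitable on either reading. On the cross-table it detects association only: assumed tables with 90% and 5% agreement give the same chi-square of 433.5, and it is significant in about 83% of studies at kappa 0.15. On the margins it is conservative, with type I error falling from about 2.4% at kappa 0.2 to 0.1% or less at kappa 0.6, where a paired test holds about 5%.

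The sizes rest on 300 vessels, one per patient, and on assumed margins and kappa values. The structural fault does not depend on them. The margins reading should not be taken as a risk of false-positive findings, since its error runs the other way. The conclusion does not extend to the therapy-strategy or lesion-level comparisons, for which the article names no test.

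**What to change.** For the vessel-level primary endpoint, replace Pearson chi-square with:

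1. the full visual-by-RFR cross-table;
2. percent agreement and unweighted kappa, each with a 95% confidence interval;
3. a Stuart-Maxwell test (marginal shift) or Bowker test (symmetry) for systematic reclassification.

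Before analysis, fix one category set for both ratings. It should include a category for vessels that meet neither RFR criterion, and a segment of exactly 25 mm should be assigned. If the therapy-strategy comparison is tested, use a paired method there too.

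Precision would be adequate. With 300 vessels, balanced margins and a true kappa of 0.6, expected agreement is 1/3 + 0.6 × 2/3 = 0.733. The simple standard error of kappa is √(0.733 × 0.267 / 300) / 0.667 = 0.038, so the 95% interval is about ±0.075.

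The cost is a short rewrite of the analysis text and minor programming, with no new patients or measurements. The category set takes more thought than the choice of test, because it must be agreed for the visual rating as well as for the RFR rating.

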**Figure 5 F5:**
[figure not shown]
Flow-chart of the proposed clinical decision-making process according to the results of physiological measurements.

In the secondary endpoints of the register, we focused on the patient population with non-ischemic FFR value. During the 1-year follow-up, the prognostic value of the focal lesions (ΔRFR > 0.05) for cardiac adverse event will be investigated in this subgroup.

The characterization of the microvascular capacity may have also paramount relevance in cases of negative (>0.80) FFR values. If the extended physiological assessment shows low CFR/FFR index or MRR value, then microvascular disease is diagnosed with the impact on appropriate specific pharmaceutical treatment (20).

This relatively simple, combined resting and hyperemic assessment can provide a comprehensive physiological evaluation of the coronary disease with important treatment consequences.

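### In patients with FFR > 0.80, the only named time-to-event comparison of ΔRFR splits it at 0.05, a cut-off not established for prognosis, and no named analysis estimates how risk changes with ΔRFR

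*Protocol article*

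**What the plan says.** All references are to the protocol article.

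- **Measurement.** ΔRFR is the difference between the RFR values at a distal and a proximal pullback marker (Invasive Coronary Physiology Assessment Protocol). It is therefore recorded on a continuous scale.
- **Outcome comparison.** Statistical Analysis plans Kaplan-Meier curves in cases with FFR > 0.80 for ΔRFR at or above 0.05/25 mm against below it, and then: "We plan to use survival analytic techniques such as a log-rank test to estimate the difference between the 2 subgroups". The sample size rests on the same contrast, "assuming 10 and 2% event rate in the two subgroups, respectively".
- **Other use of ΔRFR.** The Background plans to "determine potential alternative cut-off values using receiver-operator characteristic (ROC) analysis". Statistical Analysis repeats this, with sensitivity and specificity, against the secondary endpoint at 1 year.
- **Status of the cut-off.** The Background states: "Such a prognostic pressure-drop cut-off value for invasive hyperemic or non-hyperemic pullback measurements has not yet been established". It goes on to make testing this threshold an aim of the register. The Discussion takes the value from an iFR definition of a focal lesion (more than 0.03 in less than 15 mm) and lengthens the segment to suit stent practice. The gradient per millimetre is the same: 0.03/15 = 0.05/25 = 0.002.
- **Claims.** The Discussion says that "the prognostic value of the focal lesions (ΔRFR > 0.05) for cardiac adverse event will be investigated in this subgroup". The abstract's conclusion is wider: the register can identify a prognostic value of ΔRFR.

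**The concern.** Both planned routes end in a threshold. The two-group comparison treats a drop of 0.06 like one of 0.15, and a drop of 0.049 like none. The ROC analysis keeps the whole scale, but it ignores when events occur, gives no effect per unit of ΔRFR, and is there to select a cut-off.

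The 0.05 value was not derived from outcome data, and the plan itself expects that another value may do better. A null log-rank result would then have two explanations: ΔRFR carries no prognostic information, or 0.05 is not where risk changes. With few expected events, any information discarded within the two groups also matters for power.

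**Working it through.** **1. Inputs from Statistical Analysis and Study Objectives and Design.** One-year event rates of 10% (focal) and 2% (not focal), p < 0.05 (taken as two-sided), 80% power, required size 425, planned enrolment 300 patients of any FFR value. Implied hazard ratio: ln(0.90)/ln(0.98) = 5.2.

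**2. The plan's own figure.** The text gives no split between the groups. Assume 1:4, i.e. 20% focal.
- Pooled rate: (0.10 + 4 × 0.02)/5 = 0.036.
- Uncorrected focal group: [1.960 × √(1.25 × 0.036 × 0.964) + 0.842 × √(0.09 + 0.0196/4)]² / 0.08² = 69.6.
- With continuity correction: (69.6/4) × [1 + √(1 + 2 × 5/(69.6 × 4 × 0.08))]² = 84.5, so 85 focal and 340 not focal, total 425.

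This matches exactly, but only under the assumed split. At 1:1 the same formula gives 276 uncorrected and 324 corrected. The stated size is thus a two-group calculation.

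**3. Expected events.** With 200 FFR-negative patients and 30% focal: 60 × 0.10 + 140 × 0.02 = 8.8. With 150 and 20%: 30 × 0.10 + 120 × 0.02 = 5.4. With 300 and 50%: 150 × 0.10 + 150 × 0.02 = 18.

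**4. Analytic check (normal covariate, linear log-hazard, both assumed).** The efficiency of the cut relative to the continuous test is φ(c)²/[q(1 − q)], where q is the share above the cut c. For q = 0.30: c = 0.524, φ(c) = 0.348, efficiency 0.121/0.21 = 0.576. If the continuous test has 80% power, the cut test has Φ(2.802 × √0.576 − 1.960) = 57%. For q from 0.15 to 0.50 the efficiency is 0.43-0.64. If the cut test has 80% power, the continuous test has 94-99%.

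**5. Simulation with graded risk, calibrated to 10% and 2%.** Assumed: gamma ΔRFR (shape 1 or 2, capped at 0.20), 20-50% focal, log-hazard linear in ΔRFR, censoring at 1 year, 2000 runs per scenario.

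| FFR-negative patients | Log-rank at 0.05 | Cox, continuous ΔRFR |
|---|---|---|
| 150 | 55-60% | 69-89% |
| 200 | 64-70% | 79-97% |
| 300 | 78-87% | 90-99% |

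Within scenarios the gain is about 12-35 points over the repeated runs. With 200 patients and 30% focal it is 70% against 89%, or 19 points. Under the null (200 patients, 30% focal, 5% events, 5000 runs) the tests reject in 4.2% and 4.9% of runs.

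With normal or log-normal ΔRFR instead (4000 runs), the loss from the cut is 9-28 points at 200, 9-14 at 300 and 4-9 at 425. One example, log-normal with 50% focal: 97.8% against 70.3% at 200, and 100% against 95.5% at 425. The loss shrinks at 425 because both tests approach full power.

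**6. Simulation with a step in risk at 0.05.** In the gamma setting at 150-300 patients, log-rank has 55-87% power and continuous Cox 34-68%. The log-rank test leads by about 14-29 points. In the other setting (200-425 patients) it leads by 13-22 points; with 300 patients and 30% focal it is 85.0% against 66.6%.

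**The case against.** **The threshold is the declared hypothesis.** The Background sets out to test 0.05, and the secondary endpoints define the comparison as focal against not focal. A two-group log-rank test answers that question. This stands, and it means a continuous model can only be an addition. A reader might infer that the log-rank test is the wrong analysis and should give way; the documents do not support that.

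**ΔRFR is not analysed only after cutting.** A reader might infer that it is. The ROC analysis uses uncut ΔRFR against the same endpoint and may show that discrimination lies elsewhere than at 0.05. This stands in part: it softens the ambiguity of a null result, but gives no estimate of how risk changes over time per unit of ΔRFR.

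**The wording is open.** The phrase on techniques (such as a log-rank test) does not exclude other methods. It does confine them to the difference between the two subgroups, so any method that fits it keeps the split.

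**The rationale need not imply a gradient.** The plaque-force explanation in the Background is offered for a CT-based study that itself set a cut-off of 0.06. That is fair: the text suggests a gradient but does not establish one.

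**The simulation simplifies the groups.** Focal status depends on both drop and segment length, whereas the simulation cuts a single ΔRFR value. This stands as a limit on the figures.

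**An article may leave supportive models to a fuller plan.** True in general. Here, though, the article states the choice, a split plus a search for another split, alongside a conclusion that reaches further.

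**Conclusion.** The point holds as a mismatch between the named analyses and the abstract's claim. The survival comparison addresses 0.05, the ROC analysis looks for another cut-off, and nothing named estimates how risk changes with ΔRFR.

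A reader might infer a fixed power loss. The documents do not support one: the number of FFR-negative patients, the focal share, the ΔRFR distribution and the shape of risk are all assumptions. If risk is graded, the loss is about 12-35 points at 150-300 patients in the gamma setting, 9-28 at 200-300 in the other setting, and 4-9 at 425. The smaller sizes are the relevant ones, because 300 patients of any FFR value are planned and the FFR > 0.80 subgroup cannot contain more. If risk steps at 0.05, the sign reverses and the log-rank test gains about 14-29 points at 150-300. That is why both analyses belong in the plan. This is a worthwhile improvement to a secondary endpoint, not an error in the threshold test.

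**What to change.** Keep the Kaplan-Meier curves and the log-rank test as the test of the declared 0.05 threshold. Add to Statistical Analysis, before outcomes are examined, wording such as:

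*In patients with FFR > 0.80, a supportive Cox model for the 1-year composite endpoint will include ΔRFR as a continuous covariate, using the same per-patient value as the ROC analysis, and will report the hazard ratio per 0.01 with 95% CI. A null log-rank result will be interpreted as evidence about the 0.05 threshold and not about ΔRFR in general.*

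Using the ROC variable avoids defining a new measurement, since that analysis already needs one ΔRFR value per patient.

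Cost: a sentence or two and one more model, with no added patients or procedures. Downsides: one more secondary-endpoint analysis, an imprecise estimate from few events (about 5 to 18 in the scenarios above), and an assumed log-linear relation, which makes the model the weaker test if risk truly steps at 0.05.
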